## Abstract

**Background:**

Gingival invaginations are a common side effect of orthodontic therapy involving tooth extraction and subsequent space closure. Consequences of gingival invaginations are a jeopardized stability of the space closure and hampered oral hygiene. In a retrospective study, the factor time until initiation of orthodontic space closure after tooth extraction has been identified as a potential risk factor for the development of gingival invaginations. The aim of this pilot study is to proof this hypothesis and to enable a caseload calculation for further clinical trials. The referring question is: is it possible to reduce the number of developing gingival invaginations by initiation of orthodontic space closure after tooth extraction at an early point of time?

**Design:**

The intended pilot study is designed as a multicenter randomized controlled clinical trial, comparing the impact of two different time intervals from tooth extraction to initiation of orthodontic space closure on the development of gingival invaginations.

Forty participants, men and women in the age range of 11 to 30 years with orthodontically related indication for tooth extraction in the lower jaw, will be randomized 1:1 in one of two treatment groups. In group A the orthodontic tooth movement into the extraction area will be initiated in a time interval 2 to 4 weeks after tooth extraction. In group B the tooth movement will be initiated in a time interval >12 weeks after extraction. A possible effect of these treatment modalities on the development of gingival invaginations will be documented at the moment of space closure or 10 months +/- 14 days after initiation of space closure respectively, by clinical documentation of the primary (reduced number of gingival invagination) and the secondary endpoint (reduction of the severity of gingival invaginations).

**Trial registration:**

Universal Trial Number U1111-1132-6655; German Clinical Trials Register DRKS00004248

## Background

Gingival invaginations are a common side effect of orthodontic therapy, involving tooth extraction and subsequent space closure (Figure 1) [1]. They are defined as a cleft of the alveolar process with vertical and horizontal probing depth of at least 1 mm, occurring after tooth extraction and subsequent orthodontic space closure [2]. Their incidence is given in the range of 30% to 100% [3,4]. Consequences of this side effect are marginal bone loss, hampered oral care, and jeopardized stability of the orthodontic treatment result [1].

**Figure 1 F1:**
[figure not shown]
Exemplary illustration of a gingival invagination established after extraction of tooth 16 with subsequent orthodontic space closure.

In retrospective studies several potential risk factors for the development of gingival invaginations were evaluated, namely time from tooth extraction up to initiation of tooth movement, localization of the extraction area, smoking and duration of space closure [2,3,5]. Further, data of an animal experiment [6] suggested that early tooth movement into an extraction site could be beneficial to prevent gingival invaginations, so atrophy of the alveolar process does not proceed.

In this clinical study we try to prove the hypothesis that a timely tooth movement into an extraction area could be beneficial and prevent the development of gingival invaginations.

## Methods/Design

### Study objectives

The objective of the clinical study proposal will be to investigate the effects of a timely *versus* a prolonged space closure after tooth extraction on the incidence and severity of gingival invaginations. The study will compare two treatment groups: in group A the orthodontic tooth movement into the extraction area will be initiated in a time interval 2 to 4 weeks after tooth extraction. In group B the tooth movement will be initiated in a time interval >12 weeks after extraction. The null hypothesis will be addressed: There will be no difference of both treatment modalities on the incidence or the severity of gingival invaginations.

### Trial design

The study is designed as a multicenter pilot randomized controlled clinical trial (RCT). The study was approved by the Ethics Committee of the University Bonn, Germany (Ref. No. 061/12), Cologne, Germany (Ref. No. 12-210) and Düsseldorf, Germany (3979). A formal coordination center for clinical trials (CSSC, Bonn, Germany) will monitor the study process and assure data accuracy. Data management will be performed by an Institute of Medical Biostatistics (Institute for Medical Biometry, Informatics and Epidemiology, IMBIE, Bonn, Germany). A flow chart for the study is given in Figure 2.

**Figure 2 F2:**
[figure not shown]
**Work flow for the study.** After recruitment and screening the patients will be randomized in one of the two groups. After the tooth extraction the patients will be treated equally, but space closure will be initiated at different time points.

### Participants

Men and women whose diagnoses require tooth extraction in the lower jaw will be included in the study. Inclusion criteria are as follows:

• Orthodontically related indication for extraction of at least one premolar in the lower jaw

• Age ≥11 years up to and including 30 years

• Informed consent in words and written by the patient and his or her legal guardian

• Patient’s ability to follow the advices and to participate in the study visits

Patients with syndromes, diseases, or medication with strong impact on bone and connective tissue metabolism as well as non-compliance to the orthodontic therapy are excluded from the study (for example, medication with bisphosphonates or interferon or syndromes like cleidocranial dysplasia). A further exclusion criterion will be complications during the tooth extraction or wound healing, such as fracture of the alveolar bone, the root, or an infection during wound healing. In this case not the patient, but the extraction region will be excluded from the study.

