### Study interventions

The study intervention will be: the initiation of the orthodontic tooth movement in a time interval 2 to 4 weeks after tooth extraction (group A) *versus* tooth movement initiated in a time interval >12 weeks after extraction (group B). Once the space closure started it should be continued regardless of the applied mechanics up to the endpoint ‘space closure’ or the endpoint ‘10 months +/- 14 days after initiation of the space closure’. Space closure is defined as binding of dental floss in the contact point of the neighboring teeth in the former extraction region.

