### Screening

All patients seeking orthodontic treatment in one of the study centers are potential candidates to participate in this study. After planning the treatment the coordinator is checking the inclusion and exclusion criteria. If all criteria are fulfilled the patient will be informed about the study. Given consent to participate, the patient will be randomized.

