### Randomization

Randomization is stratified by center and organized as fax-randomization. After inclusion of a patient into the study a fax containing the screening number is sent to the coordinating center, where randomization is performed according to prepared lists for each center. The reply, containing randomization number and treatment, is also sent by fax.

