### Tooth extraction

After randomization, the patient will be referred to an oral surgeon of the study centers. Here the designated teeth will be extracted. Extraction technique, anesthesia used, and eventual complications during extraction like root fracture or flap elevation will be documented. Further, a replica of the roots of the extracted teeth will be established. Therefore the apex will be impressed in long axis into putty material for a possible replication with plaster.

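### Complications at extraction or during healing are called exclusion criteria, but they arise after randomisation and can remove randomised patients' outcomes under a rule with no common time window and no stated blinding

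*Protocol article*

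**What the plan says.** **Order of events.** Screening checks the criteria, and then: "Given consent to participate, the patient will be randomized". Under Randomization, the centre receives its answer from the coordinating centre: "The reply, containing randomization number and treatment, is also sent by fax". Under Tooth extraction: "After randomization, the patient will be referred to an oral surgeon of the study centers". So consent, randomisation and disclosure of the arm to the centre all come before extraction.

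**The exclusion rule.** Participants adds to the exclusion criteria: "A further exclusion criterion will be complications during the tooth extraction or wound healing". The examples are "such as fracture of the alveolar bone, the root, or an infection during wound healing". The unit removed is stated: "In this case not the patient, but the extraction region will be excluded from the study".

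**Sites per patient.** One site is enough to enter: "Orthodontically related indication for extraction of at least one premolar in the lower jaw".

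**Timing by arm.** Study interventions starts tooth movement 2 to 4 weeks after extraction in group A and more than 12 weeks after extraction in group B.

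**Blinding.** A blinded rater documents findings when space closure starts and at the end of the study. Nothing is said about who decides that a complication removes a region, or whether that person knows the arm.

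**The concern.** An eligibility criterion has to be checkable before allocation. Fractures at extraction and infections of the wound do not yet exist at that time, so this rule acts on the randomised set and can undo the comparability that randomisation provides.

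Three features of the rule make this more than a matter of labelling:

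- The healing period is not given a length. The two arms differ in exactly the time that passes between extraction and the start of movement.
- The list of complications is open-ended, which leaves room for judgement. The Tooth extraction section, for instance, records flap elevation as a complication, and Participants does not say whether it counts.
- Removing the region instead of the patient protects the patient count only where a second region remains.

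The primary aim is the invagination frequency in each arm, and the results are meant to support the sample size of later trials. A selectively reduced denominator would carry over into that planning.

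**Working it through.** **1. Which complications can be affected by what.**

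| Complication | When it arises | Route to a difference between arms |
|---|---|---|
| Fracture of bone or root | At extraction, after randomisation, before the arms are treated differently | Only if knowledge of the allocation influences the extraction or the decision to exclude |
| Wound infection | After extraction, over an unstated period | The same knowledge of allocation, and also a counting period that may differ by arm |

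The interval from extraction to movement is at most 4 weeks in A and more than 12 weeks in B, so it is more than 12/4 = 3 times as long in B. This is the ratio of the treatment intervals. The article does not say that it is the ratio of the periods over which infections are counted.

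**2. What would decide the bias.** Let *r* be the invagination risk over all sites of an arm, *e* the share of sites excluded and *c* the risk in the excluded sites. The rate among retained sites is

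(r − e·c) / (1 − e).

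This equals *r* only if e = 0 or c = r. With no treatment effect, the comparison stays undistorted if *e* and *c* are the same in both arms. The article gives neither quantity, so size and direction remain unknown.

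**3. Loss of patients: reproducing Table 1 first.** The significance level is not stated. I assume 5% two-sided, and exact enumeration on that basis reproduces all 12 cells.

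For p1 = 1.00 against p2 = 0.70 the calculation can be done by hand. The first arm always has no event-free patients. With *n* per arm and *k* event-free in the second arm, the two-sided Fisher p-value is 2·C(n,k)/C(2n,k).

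- n = 20: k = 4 gives 2 × 4845/91390 = 0.106; k = 5 gives 2 × 15504/658008 = 0.047. At least 5 event-free patients are needed. P(K ≥ 5), with K binomial(20, 0.30), is 76.2%, as in Table 1.
- n = 19: k = 4 gives 2 × 3876/73815 = 0.105; k = 5 gives 2 × 11628/501942 = 0.046. P(K ≥ 5), binomial(19, 0.30), is 71.8%.
- n = 18: k = 4 gives 2 × 3060/58905 = 0.104; k = 5 gives 2 × 8568/376992 = 0.045. P(K ≥ 5), binomial(18, 0.30), is 66.7%.

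**4. What those losses assume.** Losing 1 or 2 of 20 per arm means 5% or 10% of patients, with every patient having a single site. If only half had one site, the same rates would remove 0.05 × 10 = 0.5 to 0.10 × 10 = 1 patient per arm. The figures in step 3 are therefore an upper case for these assumed rates.

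Exact power is also not monotone in the arm sizes. With 19 in the 1.00 arm and 18 in the 0.70 arm, k = 4 already gives p = 3060/66045 = 0.046 (the opposite tail is more probable than the observed table and is not added). Power is then P(K ≥ 4), binomial(18, 0.30) = 83.5%. Power is thus a poor measure of the damage, and selection is the real issue.

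**The case against.** **Unequal search for infections.** A reader might infer that infections are looked for over 2 to 4 weeks in one arm and over more than 12 weeks in the other. The article does not say this. Healing starts at extraction in both arms, nothing says that counting stops when movement begins, and group A patients are still seen at recall visits every 4 to 6 weeks. If infections appear within the first two weeks, the effect of timing is small. This objection stands. What remains is that no common period is fixed, so a difference is possible and not ruled out.

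**Fractures.** These precede any difference in treatment. The article does not say whether the surgeon sees the faxed allocation. This also stands, and limits the fracture part to the influence of known allocation.

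**A figure for the bias.** One can construct a distortion: with 16/20 events in both arms, dropping one event-positive patient in A and three in B gives 15/19 = 78.9% against 13/17 = 76.5%. Nothing in the article supports those losses, so the 2.5-point gap is not evidence of size or direction.

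**Power matters little here.** The Sample size section says that the number was not chosen mainly on statistical grounds, and the test is descriptive. I accept that. The case rests on the analysis set, not on power.

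**Left to the full plan.** An article may leave analysis sets to another document. Here, however, the removal itself is stated as a fixed rule.

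**Conclusion.** The point holds in a limited form. The article sets a rule that removes extraction regions after randomisation, with the arm known to the centre, no common counting period and no stated blinding of the decision. For a single-site patient the rule removes the patient's only outcome, and so a member of the 20 per group.

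Wound-healing exclusions could differ by arm. Fracture exclusions could do so only through knowledge of the allocation. It is not shown that they will differ, and no direction or amount of bias can be given without a complication rate and the share of single-site patients.

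The fall from 76.2% to 71.8% or 66.7% rests on single-site patients throughout, losses of 1 or 2 in each arm, true rates of 1.00 and 0.70, and a 5% two-sided level. For a pilot this is a point that should be corrected, and it does not invalidate the design.

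**What to change.** In the primary analysis, keep all extraction regions of randomised patients in their assigned arm, whatever happened at extraction or during healing, and record the outcome for those regions as for any other. Report the analysis without complicated regions as a sensitivity analysis. For that analysis, define complications over one period after extraction that is the same in both arms, and have them judged without knowledge of the arm. In Participants, stop calling these events exclusion criteria.

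The cost is wording, plus outcome recording in regions that would otherwise have been dropped. The small downside is that complicated sites may add some noise to the primary estimate. The Statistical methods section separately drops patients who do not reach space closure. This change does not settle that rule, and the two must be written so that they fit together.

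Randomising after extraction is optional. It would turn fractures and early infections into true pre-randomisation exclusions, but recruitment has run since 10.12.2012. It could apply only to patients not yet randomised, would mix two procedures within the trial, and would leave later infections as post-randomisation events. It does not replace the change to the analysis set.

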### Study interventions

The study intervention will be: the initiation of the orthodontic tooth movement in a time interval 2 to 4 weeks after tooth extraction (group A) *versus* tooth movement initiated in a time interval >12 weeks after extraction (group B). Once the space closure started it should be continued regardless of the applied mechanics up to the endpoint ‘space closure’ or the endpoint ‘10 months +/- 14 days after initiation of the space closure’. Space closure is defined as binding of dental floss in the contact point of the neighboring teeth in the former extraction region.

### Screening

All patients seeking orthodontic treatment in one of the study centers are potential candidates to participate in this study. After planning the treatment the coordinator is checking the inclusion and exclusion criteria. If all criteria are fulfilled the patient will be informed about the study. Given consent to participate, the patient will be randomized.

### Sample size

The sample size is set on 20 patients per group. This sample size is not primary designated by statistical considerations. The aim of this pilot study is to gain first perceptions about behavior and distribution of study-related parameters. Obtaining data should enable a caseload calculation for future clinical trials. Possible results of a power analysis involving Fisher’s exact test comparing the incidence of gingival invaginations in both groups is given in Table 1. The differences do not reflect expected effects with both therapies; they rather demonstrate varieties which might be revealed in the chosen sample size.

**Table 1 T1:** Power for 2×20 patients calculated with a two-sided Fisher’s exact test

**p1**	**p2**				
	**0.8**	**0.75**	**0.7**	**0.65**	**0.6**
1.00	37.0%	58.5%	76.2%	88.2%	94.9%
0.95	-	29.9%	44.6%	58.9%	71.6%
0.90	-	-	24.2%	36.1%	49.2%

### Randomization

Randomization is stratified by center and organized as fax-randomization. After inclusion of a patient into the study a fax containing the screening number is sent to the coordinating center, where randomization is performed according to prepared lists for each center. The reply, containing randomization number and treatment, is also sent by fax.

### Tooth extraction

After randomization, the patient will be referred to an oral surgeon of the study centers. Here the designated teeth will be extracted. Extraction technique, anesthesia used, and eventual complications during extraction like root fracture or flap elevation will be documented. Further, a replica of the roots of the extracted teeth will be established. Therefore the apex will be impressed in long axis into putty material for a possible replication with plaster.

### Initiation of the space closure

At this point, a plaque-index [7], a bleeding index [8], probing depth of the adjacent teeth according to the Periodontal Screening Index (PSI) [9], stone models, and intraoral photos will be gathered. The coordinator of each center will activate and document the mechanic for space closure.

### Follow-up and control

During regular treatment, remaining extraction space as well as a possible adaptation of the treatment mechanics will be documented at the regular recall visits, every 4 to 6 weeks.

Eight weeks +/- 1 after initiation of the space closure another stone model and intraoral photos will be gathered.

### Endpoint - space closure or 10 months +/- 14 days after initiation of space closure

The primary end point of the study is the fulfilled space closure. If the time for space closure of a patient included in our study would exceed 10 months, this could possibly reveal problems in the treatment process. As a consequence an alternative end point was set on 10 months +/- 14 days after initiation of space closure.

This appointment obtains another plaque- and bleeding index, probing depth of the adjacent teeth, stone models, and intraoral photos. Further, the fulfilled space closure, the occurrence of gingival invaginations, their dimension and time from initiation up to space closure will be recorded.

### Outcome measurements

#### Primary outcome measurement

Primary outcome measurement will be a determination of the number of gingival invaginations at the moment of space closure. A gingival invagination is present, if there is a probing depth of at least 1 mm parallel to the occlusal plain in vestibular or oral orientation measured 2 mm caudal from the crest ‘free gingival margin to junctional epithelium’.

#### Secondary outcome measurement

Secondary endpoint will be the dimension according to LC^2^[2]. If a gingival invagination is present its entire depth will be examined using a periodontal probe (Periodontmeter from Williams 17; Hu-Fridey, Rotterdam, The Netherlands). The measurement will be taken parallel to the occlusal plane in vestibular and oral orientation and in vertical direction at a 90° angle to the occlusal plane. Maximum values from all three angles will be noted in a three-figure code, for example, probes of 3 mm in a vestibular orientation, 2 mm vertical, and 4 mm oral result in the code: 3-2-4. Complete penetration in oro-/vestibular orientation will be identified with an x and only the vertical penetration will be noted (for example, ×4).

### Blinding

To ensure quality and neutrality of the obtained data a blinded rater will perform the documentation at the time points ‘Initiation of the space closure’ and ‘End of the study’.

### Statistical methods

Primary aim of the study is the estimation of the frequency of gingival invaginations under both therapies. In group A the initiation of the orthodontic tooth movement will be performed in a time interval 2 to 4 weeks after tooth extraction *versus* tooth movement initiated in a time interval >12 weeks after extraction (group B). At the endpoints ‘space closure’ or ‘10 months +/- 14 days after initiation of the space closure’, the frequencies of gingival invaginations will be given together with 95% confidence limits. Also the odds ratio for the occurrence of gingival invaginations in both study arms will be calculated together with a 95% confidence interval. Finally, a two-sided Fisher’s exact test will be performed to descriptively compare the rates between treatment arms.

For the secondary aim, the difference in the dimensions of the gingival invaginations according to LC^2^, the median, minimum and maximum values as well as quartiles will be given. For the comparison of the values a two-sided Mann-Whitney-Wilcoxon test will be performed. Also the odds ratio in both study arms will be calculated together with a 95% confidence interval. In the case of an absence of a gingival invagination LC^2^ will be set to zero.

If some patients do not achieve the primary endpoint ‘fulfilled space closure’ and finish the study within the alternative endpoint ‘10 months +/- 14 days after initiation of space closure’ we would excluded these patients for later statistical analysis because they could possibly represent confounders.

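### Randomisation is stratified by centre but the stated between-arm comparisons pool all centres; a centre-stratified comparison is a cheap, modest improvement

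*Protocol article*

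**What the plan says.** - **Design.** The Randomization section states "Randomization is stratified by center and organized as fax-randomization" and adds that "randomization is performed according to prepared lists for each center". The abstract says that participants "will be randomized 1:1 in one of two treatment groups". The number of centres, their sizes and any blocking are not given.
- **Analysis.** Under Statistical methods the primary aim is to estimate the frequency of gingival invaginations in each arm, with 95% limits. The arms are then compared by an odds ratio with a 95% confidence interval, and a two-sided Fisher's exact "test will be performed to descriptively compare the rates between treatment arms". LC² is compared by a two-sided Mann-Whitney-Wilcoxon test. None of these is described with a centre term.
- **Size.** "The sample size is set on 20 patients per group", and "This sample size is not primary designated by statistical considerations". Table 1 gives power "calculated with a two-sided Fisher’s exact test", again without centre.
- **Incidence.** The Background reports of the condition: "Their incidence is given in the range of 30% to 100" per cent, citing published reports.

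**The concern.** Separate lists per centre make sense if centre may affect outcome, and here it may. Extraction is done by the study centres' own surgeons, each centre's coordinator activates the space-closure mechanics, and the Discussion names extraction technique and mechanics as possible influences. If centres differ and the arms are balanced within centre, the variation between centres does not contribute to the true sampling error of the difference between arms. A pooled 2×2 table still counts it. The comparison then credits itself with less precision than the design delivers.

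The stake is limited but real. The pilot exists to inform later trials, and with 40 patients any avoidable loss of information counts. The same applies to the LC² comparison.

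**Working it through.** **Inputs.** From the article: 20 per arm, 1:1, lists per centre, two-sided Fisher's test. Assumed, because not stated: alpha 0.05, three centres (three ethics committees are named) with 7/7/6 patients per arm, balance within centre, and the centre rates shown below.

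**1. Reproduce Table 1.** Power is the sum, over all 21×21 outcomes, of the two binomial probabilities wherever Fisher's p ≤ 0.05. All 12 filled cells match to 0.1 point. Example, 1.00 v 0.80: for 20 v 15 events, p = 2·C(20,5)/C(40,5) = 31008/658008 = 0.047, which rejects. For 20 v 16, p = 2·C(20,4)/C(40,4) = 9690/91390 = 0.106, which does not. Power = P(Bin(20, 0.8) ≤ 15) = 37.0%, as printed. Table 1 is therefore the unstratified exact test at 5%.

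**2. True level at nominal 5%.** The pooled tests are enumerated; the stratified tests are simulated (40,000 replicates).

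| Centre rates, both arms (%) | Fisher, pooled | Chi-square, pooled, uncorrected | Exact, stratified | CMH, uncorrected |
|---|---|---|---|---|
| 80/80/80 | 2.26 | 5.02 | 2.1 | 5.1 |
| 70/80/90 | 2.02 | 4.57 | – | – |
| 65/80/95 | 1.72 | 4.03 | 1.98 | 4.71 |
| 60/80/100 | 1.36 | 3.32 | 1.93 | 4.75 |
| 30/65/100 | 0.63 | 1.73 | 2.06 | 4.41 |

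The first row has no centre effect, so the fall from 5% to 2.26% is due to discreteness alone. At 60/80/100% ignoring centre takes off a further 2.26 − 1.36 = 0.90 point. A stratified exact test stays near 2%, so adding centre to an exact test does not restore 5%. The uncorrected CMH test does come close. With a continuity correction it runs at only 1.4% to 1.6%.

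**3. Power, with the two changes separated** (20,000 replicates; simulation error of each figure at most √(0.25/20000) = 0.35 point).

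| Group B v group A, centre rates (%) | Fisher | Pooled chi-square | CMH | Gain from leaving the exact test | Gain from centre |
|---|---|---|---|---|---|
| 70/85/100 v 40/60/80 | 30.6 | 43.5 | 45.7 | 12.9 | 2.2 |
| 50/75/100 v 20/45/70 | 34.1 | 46.8 | 57.4 | 12.7 | 10.6 |
| 60/80/100 v 20/40/70 | 57.3 | 69.3 | 76.8 | 12.0 | 7.5 |
| 75/85/95 v 50/60/70 | 31.1 | 43.7 | 43.9 | 12.6 | 0.2 |

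Total gains in the first three rows are 15.1, 23.3 and 19.5 points. Repeat runs put the centre part at about 2, 10 and 7. Comparing exact with stratified exact tells the same story: 33.1 − 30.6 = 2.5, 43.9 − 34.1 = 9.8, 65.0 − 57.3 = 7.7, and 31.4 − 31.1 = 0.3 in the last row.

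**4. Risk-difference scale.** The crude standard error exceeds the one that credits stratification by the factor √[p̄(1−p̄) / mean of p_c(1−p_c)]. At 60/80/100%:
- p̄ = (4.2 + 5.6 + 6)/20 = 0.79, so p̄(1−p̄) = 0.1659.
- The within-centre mean is (7×0.24 + 7×0.16 + 0)/20 = 0.14.
- The factor is √(0.1659/0.14) = 1.089, and the true standard error is √(2×0.14/20) = 0.118.

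The simulated average estimated standard errors are 0.125 crude and 0.118 stratified. By the same formula the excess is 2.0% at 70/80/90% and 4.7% at 65/80/95%. With no centre differences the stratified standard error is slightly larger (0.125 v 0.122).

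**5. Odds-ratio scale.** The average standard error of the log odds ratio at 60/80/100% is 0.834 crude and 0.920 centre-adjusted (Mantel-Haenszel). The adjusted one is wider by a median of 5% (65/80/95%), 9% (60/80/100%) and 25% (30/65/100%).

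**The case against.** The strongest reply is that a pooled table is defensible in a 40-patient pilot. The primary aim is the frequency per arm, the sample size does not rest on the test, Fisher's test is expressly descriptive, and its error is always on the conservative side. Table 1 uses the same test. With few patients per centre and incidence near 100%, some centres may show only events and contribute nothing to a stratified test. The article is condensed, and the analysis plan, not shown, may bring centre in. All of this stands and limits the severity. It does not remove the mismatch, because the article does name its comparisons and none of them follows the strata.

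Three stronger readings are tempting, and the documents do not support them:
- *The test runs far below 5% because centre is ignored.* Most of the shortfall is Fisher's discreteness and is present with identical centres. Comparing a pooled exact test with a stratified asymptotic one merges two changes.
- *The planned odds-ratio interval is too wide.* The precision gain belongs to the risk difference. A centre-adjusted odds ratio targets a different, conditional quantity and has a wider interval.
- *The 30% to 100% in the Background shows how far these centres may differ.* It is a range across publications. The 30/65/100% row is an extreme illustration only. Likewise, leaving the mechanics unrestricted does not show that they differ by centre.

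**Conclusion.** The stated between-arm comparisons do not follow the centre-stratified randomisation, so any precision it brings is not credited. The planned analysis is valid and conservative. Under the assumed three balanced centres, Fisher's level is 2.26% at a common 80%, about 1.4% at 60/80/100% and about 0.6% in the extreme case. Moving to an uncorrected CMH test gains about 15 to 23 power points where centres differ widely. About 2 to 10 of these come from centre and the rest from leaving the exact test. At a 20-point spread between centres, centre adds nothing.

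These sizes depend on centre numbers, balance and rates that the article does not give. Looser balance within centre would reduce the conservatism due to ignoring centre. Confidence in the size is therefore moderate. Severity is low: this is a cheap improvement, not a flaw that threatens the pilot's aim.

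**What to change.** Amend Statistical methods so that:
- the main descriptive comparison of invagination rates is a CMH test stratified by centre, stated to be without continuity correction (or the stratified exact test with mid-P);
- a centre-stratified Mantel-Haenszel risk difference with a small-sample 95% confidence interval is reported beside the planned odds ratio (simple Wald coverage was about 93.5% to 94.5%);
- LC² is compared by the van Elteren test, stratified by centre;
- the pooled Fisher's test is kept as supportive.

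The text should not claim that the odds-ratio interval narrows.

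Cost: a sentence or two, with no new patients or data, since centre is known at randomisation. Downsides: centres in which all or no patients have an event add nothing to the test, and if centres do not differ the stratified risk difference has a slightly larger standard error (0.125 v 0.122).
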